## 6 I. Summary of Changes to the Protocol

7

| Amendments to the Protocol                                             | Approval Date |
|------------------------------------------------------------------------|---------------|
| Added a third primary care site (Regent Park Community Health Centre). | 2024-02-14    |
| Sample size estimation corrected                                       | 2025-07-14    |
| Intervention revised to remove restriction on purchases with voucher   | 2025-07-14    |

## II. Original Protocol at Trial Initiation

### Effect healthy food voucher on blood glucose control in people with type 2 diabetes or prediabetes: a randomized controlled trial

#### Background & Rationale

This study is a collaboration between a non-profit organization, Community Food Centres Canada (CFCC) and researchers.

Over 4 million Canadians (or 12.4 % of households) experience food insecurity defined as the inadequate or insecure access to food due to financial constraints. The prevalence of food insecurity has increased over the last decade (11.3 % in 2008 and 12.4 % in 2012). Food insecurity is predominantly associated with living on a low income, and numerous studies have found that when income increased, food insecurity decreased. Food insecurity is more common among social assistance recipients due to an insufficient income and this applies to individuals living in cities where the cost of living is higher. People who have inadequate income employ a variety of coping mechanisms, including cutting back on food expenditures, as one of the more elastic features of their budgets, or resorting to food charity. More than 1 million Canadians (including more than 300 000 children) visited food banks in 2018. Only a portion of those who could use a food bank actually do so, due to a variety of factors from hours of operation to the stigma that is often associated with food charity. The quality, quantity and acceptability of the food provided is often inadequate and typically includes canned foods high in sugar and salt.

In the absence of income security programs that ensure adequate means to cover basic needs or widespread programs to promote food access and potentially reduce diet-related illness in low-income communities, non-profit organizations have been taking the initiative to look at the potential of scaled subsidies to both support food access and encourage healthy eating behaviours. Community Food Centres Canada (CFCC) is a leader in the non-profit sector working on food access and food justice issues in Ontario and nationally. No trial has yet been conducted to measure the health effects of these supports. The proposed trial will provide direct evidence of the effect of healthy food provision on health outcomes among people living on low incomes in Ontario with diabetes to help inform publicly funded food programs in Ontario, and Canada more broadly.

An estimated 4.4 million Canadians have diabetes or “prediabetes” and complications including an increased risk of vascular events including myocardial infarctions and strokes and microvascular complications such as visual impairment with annual health care costs estimated above \$4 billion. Standard diabetes management includes providing advice about dietary management of the disease including reducing consumption of foods with a high glycemic index such as white rice and pasta and to increase consumption of high fibre foods such as vegetables, and this type of advice has been proven in trials to reduce blood glucose levels and

proven the progression of diabetes. Individuals with a low income are less likely to adhere to dietary guidelines and are at increased risk of diabetes complications.

Food subsidies have been extensively piloted and evaluated in the United States. Facilitating access to healthy foods could free up money for the purchase of other needed goods or services. Even if a Basic Income – or other measures to ensure a sufficient income – is instituted in the future and it remains at a sufficient level indefinitely, receiving essential free goods will free up family income for other uses. There are already publicly funded programs to provide people with free tangible goods that are expected to promote health such as “baby boxes” in Finland, syringe distribution to intravenous drug users, and free food for pregnant women in Quebec. There are also programs to subsidize food for people living in remote communities in Canada.

## **Objectives and Specific Aims of the Project**

In adults with type 2 diabetes or “prediabetes” experiencing either food insecurity or trouble making ends meet, what is the effect of a \$65 food voucher monthly on hemoglobin A1c values after 6 months?

## **Inclusion/Exclusion Criteria**

Participants will be adult (age >19 years) patients of the two participating primary care who have either “pre-diabetes” (A1c 6.0 to 6.4) or diabetes (A1c  $\geq$  6.5) based on bloodwork done in the last 3 months and who either score 2 or above on the six-item food insecurity instrument or who report trouble “making ends meet”. We will exclude people who live with a current study participant (to avoid contamination), people who are palliative (have a life expectancy < 6 months), people with multiple (>3) life-threatening allergies to common foods, people who require total parenteral nutrition, and people with a blood dyscrasia that interferes with hemoglobin A1c testing (anemia due to iron deficiency, B12 deficiency and folate deficiency). We will also exclude individuals with very poorly controlled diabetes (A1c > 11) as interventions other than food such as medicines may be the most important interventions. We will also exclude individuals with very poorly controlled diabetes (A1c > 11) as interventions other than food such as medicines may be the most important interventions.

## **Recruitment & Enrollment**

Enrollment will take place within the two primary care sites in Toronto, Ontario (population 2.3 million). Notices of the study will be posted in waiting rooms and examination rooms and study brochures will also be distributed around the primary care sites. The study team will attend team meetings to make clinicians aware of the study. We will facilitate searches of electronic health records to identify potentially eligible patients and will provide clinicians with a list of

potential participants. We will ask clinicians to contact potential participants and, if they are interested in learning more about the study, clinicians will share the patient's phone number or email address with the research assistant or coordinator who will contact the patient to confirm eligibility and consent. If consent is provided, the research assistant will enter participant details in the electronic case report form that will also randomize the participant to one of the two groups. Randomization will be achieved by a web-based interface. After research personnel enter identifying details, the participant will be randomized to one of the two groups. Overall blinding is not possible because participants in the intervention group will be provided with voucher. Outcome assessors will be blinded to the group of allocation.

We expect to recruit at least 1 participant per working day and thus recruiting 390 participants may take up to 19 months. The St Michael's Academic Family Health Team is made up of six physical sites in downtown Toronto and serves approximately 45 000 patients. South Riverdale Community Health Centre is made up of six physical sites and serves approximately 10 000 patients. The collective size of the patient population across sites is approximately 55,000 and the prevalence of diabetes is 7.3 % so we estimate that there are at least 4,000 patients with diabetes and patients with diabetes typically attend appointments every 3 to 6 months and thus there are approximately 12,000 visits for diabetes each year. Based on previous waiting room surveys of patients, we estimate that at least 25 % will meet the inclusion criteria so there should be at least 1,000 patients eligible to participate. If the recruitment rate is slower than expected, we will expand the study to additional sites.

The sample size estimation is based on the power to detect a clinically important 0.4 % difference between groups in the primary outcome of the change in hemoglobin A1c. The change in hemoglobin A1c will be treated as a continuous variable. Based on previous trials, we expect a mean change in hemoglobin A1c in the control group of 0 with a standard deviation of 1.3 to 2 %.(38) To detect a 0.4 % absolute difference, a sample size of 332 to 346 is required ( $\alpha$  0.05, power 80 %). Assuming a 10-15 % rate of drop-out or missing data (e.g. missing hemoglobin A1c measurement), 390 participants (195 in each group) are needed. (The sample size estimation was revised to correct errors in the original protocol.)

Based on previous trials in this setting in similar populations, we expect a loss to follow up rate up to 15 %. The primary care population is relatively stable with only a small fraction (< 5 %) leaving the practice each year.

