### **Design, Data Collection & Analysis**

The study is an individual participant, 1:1 allocation, two-arm parallel randomized controlled trial. Allocation will be unblinded to participants and clinicians; outcome assessors and adjudicators will be blinded. Randomization will be stratified by condition: “pre-diabetes” (A1c 6.0 to 6.4) versus diabetes (A1c  $\geq$  6.5).

The trial design including the outcomes will be publicly registered and results reported according to CONSORT and TIDier guidance. We will make individual level participant data available when the study is complete (no identifying information about participants).

An established community guidance panel will contribute to developing the plan to implement the intervention and provide direction in study processes, interpretation and recommendations and may also identify potential additions to the study outcomes.

Study personnel will send the clinicians of participants in each group messages, through the electronic health record, at three, four and five months after randomization reminding them that the patient may be due for a hemoglobin A1c measurement. We will also contact participants by phone and email to remind them about having their hemoglobin A1c checked at 5 months.

The intervention period is six months. We will administer a survey after six months which can be completed by phone, by email, in person during a clinic visit or in person at home and will take approximately 15 minutes to complete. A subset of 20 randomly selected intervention group participants will be prompted to report all foods and beverages consumed the prior day using a validated self-administered 24-hour recall as part of this survey. In a separate subset of 20 purposefully selected intervention group participants, we will conduct interviews to capture the experience of the intervention for qualitative analysis. Prior to contacting participants to complete the survey, we will send a reminder notice by email or mail. Participants in both the intervention and control groups will be compensated \$15 for completing the 6 month follow up survey. The subset of 20 participants will be compensated an additional \$20 when they complete the one-on-one interview which will take approximately 20 minutes.

Hemoglobin A1c will be assessed by a review of the electronic primary care record or based on laboratory testing for study purposes if not ordered for clinical purposes.

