ask participants in the intervention group how often they accessed the food retailer, about their participation in educational and community building activities, about wasted food and about whether they would have wanted other foods to be provided.

We will perform a cost-effectiveness analysis from a societal perspective that considers direct and indirect costs of the intervention and direct and indirect effects including changes in healthcare utilization. We will assess the economic implications of the potential effects of the intervention including costs associated with primary care, emergency department use, and complications of diabetes based on previous studies of the association between hemoglobin A1c and health outcomes.

We will report demographic characteristics collected at the time of enrollment including age, sex, gender, education level, household income, income source, ethnicity, and medical comorbidities.

We will employ an intention to treat analysis. The primary analysis of the follow-up A1c (follow-up measurement) will be adjusted for baseline hemoglobin A1c and analysed using analysis of covariance (ANCOVA). Binary outcomes will be compared between groups using risk differences with 95% confidence intervals, and chi-squared tests to derive two-sided p-values. Continuous outcomes will be compared between groups using difference in means with 95% confidence intervals, and t-tests to derive two-sided p values. Count outcomes will be analysed using rate ratios from quasi-Poisson models with 95% confidence intervals and two-sided p-values, which will be adjusted for baseline values whenever available. Ordinal outcomes will be analyzed using ordinal regression.

Randomization will be stratified by site. We will report both the unadjusted analysis for the primary outcome and the analysis adjusted for age, sex, whether or not prescribed diabetes oral medicines at baseline, and whether or not prescribed insulin at baseline.

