## 7. Sample size

The sample size was estimated based on the power to detect a clinically important 0.04 difference between groups in the primary outcome of the change in hemoglobin A1c. Based on previous trials, we expect a mean change in hemoglobin A1c in the control group of 0, with a standard deviation of 0.013 (1.3%). To detect a 0.004 (0.4%) absolute difference, a sample size of 332 (166 in each group) is required ( $\alpha$  0.05, power 80%). Assuming a 15% rate of drop-out or missing data (e.g. missing hemoglobin A1c measurement), 390 participants (195 in each group) are needed. A total of 390 participants were recruited, with 194 allocated to the intervention group and 196 allocated to the control group.

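### The protocol's sample size range does not follow from its SD range (an SD of 2% needs 786, not 346; power with 332 analysed is about 44%), and SAP section 7 misstates the target difference tenfold

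*Combined protocol and SAP*

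**What the plan says.** The protocol's sample size paragraph (under Recruitment & Enrollment) works from the change in HbA1c and supposes no average change among controls. On the spread and the resulting size it states: "standard deviation of 1.3 to 2 %.(38) To detect a 0.4 % absolute difference, a sample size of 332 to 346 is required". This is at alpha 0.05 and 80% power. Allowing for 10 to 15% drop-out or missing data, it arrives at 390 randomised, 195 per group. The paragraph ends by noting that the estimate was revised to correct errors in the original protocol, and the summary of changes lists that correction as approved on 14 July 2025.

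SAP section 7 (SAP dated 9 March 2025) works in proportions. It opens: "The sample size was estimated based on the power to detect a clinically important 0.04 difference between groups". It then takes a single SD of 0.013 (1.3%), gives the difference as 0.004 (0.4%), and obtains 332 participants (166 per group) and 390 after 15% loss. It reports 390 recruited, 194 to intervention and 196 to control.

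**The concern.** Required sample size rises with the square of the SD. Going from 1.3% to 2% multiplies the SD by 2/1.3 = 1.54 and the sample size by 1.54² = 2.37. The protocol's range rises by only 346/332 = 1.04. The two ranges cannot both be right, and the inconsistency sits in text presented as a correction.

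The SAP and protocol also disagree on the SD (1.3% alone against 1.3 to 2%), and the SAP gives two values, a factor of ten apart, for the same target difference.

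At stake is how a null primary result will be read. A reader told that the trial had 80% power for 0.4% across SDs up to 2% would take a null result as fairly strong evidence against an important effect. At the upper end of that SD range the trial would miss a true 0.4% difference more often than it would find it.

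**Working it through.** **Inputs**

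- Difference 0.4 percentage points; SD of change 1.3 to 2; alpha 0.05; power 80%; loss 10 to 15% (protocol, sample size paragraph).
- Design: "1:1 allocation, two-arm parallel randomized controlled trial".
- Sidedness is not stated in the sample size paragraph. Two-sided is assumed, in line with the protocol's analysis text for continuous outcomes ("t-tests to derive two-sided p values").

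**Formula**

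n per group = 2 × (1.960 + 0.842)² × (SD/0.4)², where (1.960 + 0.842)² = 7.849 before rounding of the two terms.

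**1. The plan's lower figure reproduces.** SD 1.3: 2 × 7.849 × (3.25)² = 165.8, so 166 per group and 332 in total. With 15% loss, 332/0.85 = 390.6, which agrees with 390.

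**2. The upper figure does not.** SD 2: 2 × 7.849 × 5² = 392.4, so 393 per group and 786 in total. With loss this becomes 786/0.90 = 874 or 786/0.85 = 925. The t-test version gives 394 per group.

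**3. What 346 corresponds to.** With 173 per group, SD = 0.4 × √(173/2) / 2.802 = 1.33.

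**4. Other readings of SD 2.** A one-sided test gives 620. An SD of 1.3 in one arm and 2 in the other gives (1.3² + 2²) × 7.849/0.16 = 279.1, so 280 per group and 560 in total. Neither gives 346.

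**5. Power for 0.4%** (two-sided t-test, unadjusted comparison of change):

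| SD of change | 332 analysed (15% loss) | 390 analysed (no loss) |
|---|---|---|
| 1.3 | 80% | 86% |
| 1.5 | 68% | 75% |
| 1.8 | 52% | 59% |
| 2.0 | 44% | 50% |

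At 10% loss (390 × 0.90 = 351 analysed), power at SD 2 is 46%.

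**6. Detectable difference** at 80% power with 166 per group and SD 2: 2.802 × 2 × √(2/166) = 0.62 percentage points.

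**7. Loss allowance for the plan's own 346.** 346/0.90 = 385 fits within 390, but 346/0.85 = 408 does not. 390 covers 346 only up to 1 − 346/390 = 11.3% loss, so it does not cover the full 10 to 15% range.

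**8. SAP units.** With SD 0.013, a difference of 0.004 gives 166 per group, matching the SAP. A difference of 0.04 would give 2 × 7.849 × (0.013/0.04)² = 1.7, so 2 per group. The SAP's 332 was therefore not computed from 0.04.

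**The case against.** The operative number is sound. With SD 1.3% and 15% loss, 390 is right, the SAP's calculation is correct, and 390 were recruited. The error is confined to the upper end of one range and one misplaced decimal. This stands as a limit on the finding: the planned size is inadequate only for SDs above about 1.3%. It does not rescue the protocol's claim, which explicitly extends to 2%.

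The power figures are for an unadjusted comparison of change, whereas the protocol's primary analysis is ANCOVA adjusted for baseline HbA1c, which is normally more efficient. This also has force. The documents give no baseline to follow-up correlation, so one must be assumed. With equal variances at the two times and correlation r, the residual variance is the change-score variance times (1 + r)/2. For r = 0.7, 0.5 and 0.3, power with 166 per group is 75%, 80% and 85% at SD 1.5, and about 50%, 56% and 62% at SD 2. Adjustment could thus close the gap at SD 1.5 but not at SD 2. For 346 to give 80% power at SD 2, covariates would have to remove 1 − (1.328/2)² = 56% of the variance of the change, which neither document claims. The restated figures should be labelled as unadjusted.

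The SD rests on a cited source not available here, so the documents cannot show whether the 2% or the 346 is the slip. That is a reason to word the correction conditionally on the SD, which then holds either way.

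Finally, a null result can be judged by its confidence interval, and SAP 8.2 will report the SD of change. That limits the harm, but does not justify leaving a wrong power statement in text labelled as corrected.

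**Conclusion.** The concern holds. From the protocol's own inputs, 332 is right for SD 1.3%, but SD 2% needs 786 evaluable participants, not 346. Power for 0.4% with 332 analysed falls from 80% at SD 1.3% to about 44% at SD 2%, and is only about 50% there even if all 390 are analysed. These figures assume a two-sided 5% test, equal arms and no baseline adjustment. Under assumed correlations of 0.3 to 0.7, adjustment raises the SD 2% figure to about 50 to 62%, still well short of 80%.

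The SAP's 0.04 is a tenfold slip that does not affect its sample size, but it misstates the clinically important difference in the document that governs the analysis. Both errors need correcting.

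**What to change.** No further enrolment is needed; restate the figures.

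- **Protocol, sample size paragraph:** delete the 332 to 346 range and replace it with a statement conditional on the SD, for example: *390 randomised (about 332 analysed after 15% loss) gives 80% power for a 0.4 percentage point difference if the SD of change is 1.3%; power falls to about 68% at SD 1.5% and 44% at SD 2% (two-sided alpha 0.05, unadjusted comparison of change).* Check the 2% against the cited source while doing so.
- **SAP section 7:** replace 0.04 with 0.004 (0.4 percentage points) and carry the same SD and power statement, so that the two documents agree.

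The cost is wording in two places and a less favourable stated power. Design, conduct and analysis are unchanged.

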## **Interventions**

Participants allocated to the control group will continue their usual clinical care, that includes information from clinicians about nutrition, and their usual access to food. Patients diagnosed with diabetes or who are at high risk of developing diabetes are typically offered group educational sessions about diabetes and non-pharmaceutical management approaches including diet and exercise. There is also an option to meet one-on-one with a registered dietitian and a registered nurse to discuss diet and exercise. Participants allocated to the

intervention group will receive a monthly subsidy of \$65 for healthy food (or \$85 for participants who are members of households with more than five individuals) for fruit and vegetables every month for six months, and they will continue their usual clinical care that includes information from clinicians about nutrition. The “food prescription” voucher will be provided in the form of digital grocery cards redeemable at local retail stores - these cards were not restricted to the purchase of fresh and frozen fruits and vegetables (although that had been the earlier plan). All participants will still have access to their other regular food sources.

### **Design, Data Collection & Analysis**

The study is an individual participant, 1:1 allocation, two-arm parallel randomized controlled trial. Allocation will be unblinded to participants and clinicians; outcome assessors and adjudicators will be blinded. Randomization will be stratified by condition: “pre-diabetes” (A1c 6.0 to 6.4) versus diabetes (A1c  $\geq$  6.5).

The trial design including the outcomes will be publicly registered and results reported according to CONSORT and TIDier guidance. We will make individual level participant data available when the study is complete (no identifying information about participants).

An established community guidance panel will contribute to developing the plan to implement the intervention and provide direction in study processes, interpretation and recommendations and may also identify potential additions to the study outcomes.

Study personnel will send the clinicians of participants in each group messages, through the electronic health record, at three, four and five months after randomization reminding them that the patient may be due for a hemoglobin A1c measurement. We will also contact participants by phone and email to remind them about having their hemoglobin A1c checked at 5 months.

The intervention period is six months. We will administer a survey after six months which can be completed by phone, by email, in person during a clinic visit or in person at home and will take approximately 15 minutes to complete. A subset of 20 randomly selected intervention group participants will be prompted to report all foods and beverages consumed the prior day using a validated self-administered 24-hour recall as part of this survey. In a separate subset of 20 purposefully selected intervention group participants, we will conduct interviews to capture the experience of the intervention for qualitative analysis. Prior to contacting participants to complete the survey, we will send a reminder notice by email or mail. Participants in both the intervention and control groups will be compensated \$15 for completing the 6 month follow up survey. The subset of 20 participants will be compensated an additional \$20 when they complete the one-on-one interview which will take approximately 20 minutes.

Hemoglobin A1c will be assessed by a review of the electronic primary care record or based on laboratory testing for study purposes if not ordered for clinical purposes.

